**Methods:**

This study is a randomized controlled trial (RCT) with blinded assessment comparing Standard Care (SC) with a novel Family Nurture Intervention (FNI). FNI targets preterm infants born 26-34 weeks postmenstrual age (PMA) and their mothers in the NICU. The intervention incorporates elements of mother-infant interventions with known efficacy and organizes them under a new theoretical context referred to collectively as calming activities. This intervention is facilitated by specially trained Nurture Specialists in three ways: 1) In the isolette through calming interactions between mother and infant via odor exchange, firm sustained touch and vocal soothing, and eye contact; 2) Outside the isolette during holding and feeding via the *Calming Cycle*; and 3) through family sessions designed to engage help and support the mother. In concert with infant neurobehavioral and physiological assessments from birth through 24 months corrected age (CA), maternal assessments are made using standard tools including anxiety, depression, attachment, support systems, temperament as well as physiological stress parameters. Quality of mother-infant interaction is also assessed. Our projected enrolment is 260 families (130 per group).

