Mothers complete initial assessments after consent and families are then assigned to the FNI intervention group or the SC group using a randomized block design. For randomization, six group assignment cards (3 FNI: 3 SC) are placed in envelopes and sealed. The envelopes are shuffled, numbered and placed in a packet prior to use. The RA withdraws an envelope from the packet to determine group assignment. Within 1 to 2 days of consenting, mothers assigned to the FNI group meet with a Nurture Specialist (NS) designated to facilitate the intervention and begin to carry this out, as described in the Intervention Methods section below. Mothers of infants assigned to the SC condition receive NICU standard care as described in the Standard Care section below. Twins are "clustered" for purposes of randomization, with both infants being assigned to the same group along with the mother.

To determine the total sample size necessary to ensure statistical power of not less than 0.8 to detect differences between group means, we considered the detectable difference for each of the primary outcome variables that would be of interest for a successful study result. Our experience and that of others suggested that effect sizes within the 'medium' range would be achievable (i.e., 0.4 to 0.6). Therefore, given the two independent samples created within the RCT design, assuming a significance level of α = .05 for a two-tailed test, we estimate that we will have at least 80% power (1-*β *≥ .80) to detect a difference between groups for effect sizes and total sample sizes as described in Table 1. Experience with the pilot study suggests that we could expect attrition at a rate as high as 40%. To accommodate this, we intend to recruit a total of N = 260 participants from which a final sample size sufficient to detect all differences of interest should be achieved.

**Table 1 T1:** Power analysis

Outcome Measure	PMA	Reference Population *μ *(*σ*)	Detectable Difference |*μ*_FN_-*μ*_SC_|	Effect Size *d*	Total N Required

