### Planned analyses

Descriptive statistics will be derived for all predictor and outcome variables. Family socio-demographic characteristics are not expected to differ by study group, but significance tests will be conducted to confirm the success of the randomization process. Outcomes for the two study groups including infant EEG measures, stress and development, and maternal stress and depression will be compared at each measurement interval (intake, term, 4, 12, 18, and 24 months CA) using independent t-tests for differences between means for continuous data and chi-squared tests for differences between proportions for categorical data. The Bonferroni correction will be applied to account for multiple testing. Longitudinal analyses assessing differences over time will be conducted using repeated measures ANOVA for continuous data and Kruskal-Wallace or Friedman's adaptation of this test for non-parametric data. Generalized linear models will be used to assess the variability in infant development, as measured by Bayley-III Scales at 18 months CA. This variability is explained by repeated maternal and infant psychological and neurological factors after controlling for baseline family socio-demographic characteristics.

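### Single-step Bonferroni is valid, but the Holm step-down would reject at least as often at the same family-wise error rate: a one-sentence improvement, not an error

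*Protocol article*

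**What the plan says.** Under Planned analyses, the two groups are compared on infant EEG, stress and development and on maternal stress and depression. These outcomes "will be compared at each measurement interval (intake, term, 4, 12, 18, and 24 months CA"), by t-tests or chi-squared tests. The multiplicity rule is one sentence: "The Bonferroni correction will be applied to account for multiple testing". The article does not give the number of tests in the family, and it does not claim that Bonferroni is the most powerful choice.

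The sample-size paragraph under Participants works outcome by outcome, "assuming a significance level of α = .05 for a two-tailed test", and aims for "statistical power of not less than 0.8 to detect differences between group means". It warns that "we could expect attrition at a rate as high as 40" per cent and sets the recruitment target at 260.

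**The concern.** Bonferroni compares every p-value with α/m. Holm orders the p-values and compares the smallest with α/m, the next with α/(m−1), and so on, stopping at the first failure. No Holm threshold is below α/m, so Holm never rejects less. It controls the same family-wise error rate and needs no assumption about correlation.

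Holm gains most when several effects are real, and that is what this trial hypothesises. The primary hypotheses under Methods and Design predict benefit on EEG power and on neurobehavioural function near term and at 18 months, and the sample-size paragraph wants a final sample large enough for every difference of interest. At stake is some power for individual outcomes, given up with no gain in error control.

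**Working it through.** **Inputs.** Table 1 gives differences and standard deviations, so d = difference/SD:
- EEG: 0.2/0.434 = 0.461
- NNNS: 1.0/1.73 = 0.578 (one illustrative subscale of 13, by the table's footnote)
- Bayley-III: 6.0/14 = 0.429 (the table prints .41, but its N of 174 matches 0.429)

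Retained sample: 260 × 0.60 = 156, or 78 per arm.

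**Plan's own figures first.** A two-sample t-test at two-sided .05 with 80% power needs total N of 150, 96 and 174 for these d. All three agree with Table 1.

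**Assumptions.** The article does not give m. The base case takes m = 3, the outcomes named in the primary hypotheses, treated as independent, with all effects real and infants independent.

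**Bonferroni and Holm at m = 3** (200,000 simulated trials, t-tests, 78 per arm). Bonferroni uses .05/3 = .0167 throughout; Holm uses .0167, .025 and .05 in order.

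| | EEG | NNNS | Bayley-III | All three |
|---|---|---|---|---|
| Bonferroni | .676 | .882 | .601 | .358 |
| Holm | .780 | .925 | .721 | .573 |
| Gain (points) | 10.4 | 4.3 | 12.0 | 21.5 |

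Check on the last column: under independence, Bonferroni gives .676 × .882 × .601 = .358. Holm cannot exceed the product of the unadjusted powers at 78 per arm, .816 × .948 × .758 = .586, and .573 lies just below it.

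Under the global null, the family-wise error is .049 for both procedures.

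**Correlation of .3.** All three significant: .419 against .612, a gain of 19.3 points, slightly less than under independence.

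**How the gain changes with the scenario** (78 per arm, independent tests):
- Two of three effects real: about 2 to 5 points for each real outcome.
- One of three real: near zero (EEG 68.8% against 68.9% in a normal-approximation run).
- m = 4, adding HRV, all four real: EEG .639 to .755 and Bayley-III .559 to .694, that is 11.6 and 13.5 points.
- m = 7, the number of measures listed under Primary and Secondary Outcome Measures, with the same three real and the rest null: about 2 to 3 points.
- m = 13, same three real and the rest null: about 1 point.
- At least one rejection: identical in every scenario (.985 for both in the base case), because Holm's first step is also α/m.

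**Limit.** Holm cannot exceed the unadjusted power for an outcome. For Bayley-III at 78 per arm that is .758, so no choice of multiplicity procedure reaches 80% there. EEG reaches .780 in the base case.

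**The case against.** The strongest objection is that Bonferroni is valid and pre-specified, so preferring Holm is a matter of taste. The first half stands: nothing in the article is misstated or contradictory here. The remark could also be made of any trial that uses Bonferroni. What remains is that the swap costs little in a trial with little power to spare.

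Two advantages of Bonferroni are real. It has simple simultaneous confidence intervals. It also lets each outcome be judged at a fixed α/m as results arrive from term to 24 months, whereas Holm's later steps need the other p-values. Both weigh little here: Planned analyses mentions no simultaneous intervals, and under Holm an outcome with p at or below α/m can still be declared at once.

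The base case is also favourable. Three tests, all with real effects, is close to the best setting for Holm, and larger families with many null tests shrink the gain to a point or so.

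Three stronger readings are tempting and are not supported:
- *Bonferroni loses power for nothing.* The interval and timing advantages are something, if modest.
- *Bonferroni loses most because the outcomes move together.* If that means correlation, the gain falls slightly as correlation rises. It is the number of real effects that matters.
- *Holm would cure the power shortfall.* The article says "we estimate that we will have at least 80% power" on the basis of an unadjusted .05. That calculation and the attrition are separate matters, and Holm does not restore 80%.

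**Conclusion.** The point holds as a cheap improvement and not as an error. Holm's rejections always include Bonferroni's, at the same family-wise error rate. In the base case (family of EEG, NNNS and Bayley-III, all Table 1 effects real, independent outcomes, 78 per arm) the gain is about 10, 4 and 12 points per outcome. For all three together the chance rises by about 21 points, from 36% to 57%.

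That size rests on the assumed family and on all effects being real. It falls to a few points or to nothing when few effects are real or the family is large, but it is never negative.

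**What to change.** Replace the Bonferroni sentence in Planned analyses with: *Within the family of primary outcomes, p-values will be adjusted by the Holm step-down procedure at two-sided family-wise alpha .05.* List the members of that family where the rule is applied. State that the reported 95% confidence intervals are unadjusted, since such an interval can exclude zero while the Holm-adjusted p-value exceeds .05. If the sponsor prefers to keep Bonferroni, one line giving the reason would suffice.

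The cost is one sentence and no extra participants, and the change should be made before any group comparison is run. The downsides are that Holm has no simple matching simultaneous intervals, and that outcomes with p above α/m may have to wait for later visits before they can be declared.

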To reduce the bias potentially associated with a randomized controlled trial of this size in a modern NICU, the following criteria developed by the Cochrane Collaboration for evaluation of intervention studies [87] will be adopted: (1) the sequence generation of allocating subjects will be random; (2) group designation will be concealed until after consent is obtained and the first set of questionnaires is administered; (3) the blinding of participants, research and clinical staff, and outcome assessments will be achieved to the extent possible; 4) outcome data will be complete; (5) outcome reporting will not be selective.

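### The planned rank tests cannot compare FNI with SC over time, and classical repeated measures ANOVA keeps only fully observed subjects when up to 40% attrition is expected

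*Protocol article*

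**What the plan says.** All references are to the protocol article.

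- **Planned analyses, between-group step.** The arms are compared at each interval ("intake, term, 4, 12, 18, and 24 months CA") "using independent t-tests for differences between means for continuous data", with chi-squared tests for categorical data.
- **Planned analyses, longitudinal step.** "Longitudinal analyses assessing differences over time will be conducted using repeated measures ANOVA for continuous data". Where a rank method is needed instead, the section names "Kruskal-Wallace or Friedman's adaptation of this test for non-parametric data". The article names neither a group-by-time term nor a group contrast for this step.
- **Participants (sample size paragraph).** "Experience with the pilot study suggests that we could expect attrition at a rate as high as 40" per cent, with recruitment set at 260. The Abstract gives this as 260 families, 130 per group.
- **Twins.** Only the first-born twin is assessed at the 4- and 12-month visits.
- **Potential limitations.** Among the risk-of-bias criteria to be adopted is that "outcome data will be complete".
- **Table 1 and Primary and Secondary Outcome Measures.** Cortisol is the only Table 1 outcome given by median and interquartile range (2.4; 1.6 to 4.1, in the maternal row). The infant cortisol response at 4 months is listed as primary. Table 2 schedules cortisol repeatedly to 24 months.

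**The concern.** The trial's hypotheses all compare FNI with SC, so a longitudinal analysis is useful only if it carries that comparison. The two rank tests named do not. A Friedman result would show whether scores change between visits. In growing infants they will, whatever the arm.

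The continuous-data method has a different weakness. Classical repeated measures ANOVA needs a value at every visit in the analysis, and the article itself expects heavy loss. Families seen at some visits but not all would contribute nothing, and second-born twins would drop out by design from any visit-based analysis spanning 4 or 12 months. At stake are precision, possible bias, and a usable longitudinal answer for skewed outcomes.

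**Working it through.** **1. What each test compares**

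| Method named | Group term? | Time element? | Gives FNI-SC over time? |
|---|---|---|---|
| Friedman | No | Yes, within subject | No |
| Kruskal-Wallis, two arms, one visit or change score | Yes | No (or only through the change score) | No; a valid single comparison |
| Repeated measures ANOVA with arm as between-subject factor | Yes | Yes | Yes, on complete subjects |

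**2. Simulation of the methods**

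Assumptions: 78 per arm (156 retained), 5 visits, correlation 0.5 between visits, 2,000 runs per scenario, two-sided 5% level.

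Friedman, arms pooled:
- Constant 0.45 SD difference between arms: rejects 5.3%.
- Opposite trends in the two arms: rejects 4.0%.
- The same trend in both arms, no treatment effect: rejects 98.8%. A separate run with 4 visits and a common 0.45 SD trend gave 99.6%.

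Kruskal-Wallis at one visit with a 0.45 SD difference there: power 0.78.

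Repeated measures ANOVA on complete subjects:
- Group-by-time under the null: rejects 5.1%.
- Difference growing from 0 to 0.45 SD: group-by-time power 71%.
- Constant 0.45 SD difference: group main effect power 96%.

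**3. Subjects left for classical ANOVA**

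From the article's own figures: 260 × (1 − 0.40) = 156 families. This is a ceiling at that attrition rate, because it assumes those who stay miss no visit.

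The rate of sporadic missed visits is not given. As an assumed range, with 5 follow-up visits:
- 5% per visit: 156 × 0.95^5 = 121.
- 10% per visit: 156 × 0.90^5 = 92.

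Two-group t-test power at d = 0.45 is 0.80 with 156, 0.69 with 121 and 0.57 with 92. The number of visits depends on the outcome (Bayley-III has two, at 18 and 24 months), so the loss does too.

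**4. Observed data discarded**

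Assume the 40% accrues evenly over 5 visits. Numbers seen are then 239.2, 218.4, 197.6, 176.8 and 156.0, which sum to 988 records. Complete-case analysis uses 156 × 5 = 780, and 780/988 = 79%. About 21% of collected records go unused.

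**5. Bias**

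Assumptions: two visits, correlation 0.6, true effect zero, about 40% dropout. In one arm dropout depends on the earlier value (log-odds slope 0.5 to 0.8); in the other it does not. Completers show a spurious difference of 0.11 to 0.17 SD, while a likelihood-type estimate using all data shows about 0. When dropout is unrelated to earlier values in both arms, completer bias is about 0.

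**The case against.** The main treatment comparison lies elsewhere. The per-visit t-tests and chi-squared tests compare the arms directly, most primary outcomes are tied to one time point, and Table 1 is powered for a difference in means. The longitudinal sentence is additional and speaks only of change over time. If within-arm change was meant, Friedman is valid. Missing-visit rules are normal detail for an analysis plan that is not shown. These points stand and limit the reach of the finding. They do not rescue the rank tests: read as a within-arm test, Friedman gives no treatment comparison, and the methods are named in the article rather than left open.

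Some stronger readings are tempting but unsupported:

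- **That none of the longitudinal methods can answer the question.** This is wrong for repeated measures ANOVA, as step 2 shows.
- **That Kruskal-Wallis inflates type I error.** It does so, to 21–25% in simulation, only if repeated visits are pooled as independent rows. The article proposes no such pooling.
- **That only about 53% (138 of 260) would be complete.** This assumes 10% independent missingness at six points, and one of those is intake, where STAI and CES-D are completed before assignment.
- **That dropout linked to distress or illness must bias the result.** With no treatment effect and the same dropout mechanism in both arms, the expected completer difference is zero.
- **That unequal visit spacing breaks sphericity.** Spacing alone does not, and the between-subject group test does not rely on sphericity.

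**Conclusion.** The point holds in two parts of unequal strength.

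The rank tests are a poor choice as stated. Friedman carries no arm comparison, and Kruskal-Wallis compares arms without a time element. This follows from the structure of the tests; the simulation only illustrates it. It bears most on cortisol, if its median-and-IQR summary means it will be analysed non-parametrically, which is an inference.

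Repeated measures ANOVA answers the right question inefficiently. It keeps at most 156 of 260 families at 40% attrition and loses second-born twins where 4- or 12-month visits enter. Any loss below 156 rests on assumed rates of missed visits. The 0.11 to 0.17 SD bias rests on dropout that depends on earlier outcomes differently by arm, for which the article gives no evidence either way.

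The completeness criterion also cannot stand unqualified beside expected attrition of up to 40%. The change should be made, but the per-visit comparisons are not undermined by it.

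**What to change.** 1. State the group-by-visit contrast as the longitudinal target.
2. Estimate it with a likelihood-based linear mixed model using every available visit. Include group, categorical visit and group-by-visit, allow for within-subject correlation, and add a random effect for family where both twins contribute. Adjust for the baseline value only where the outcome is collected before assignment, which in Table 2 means STAI and CES-D.
3. For skewed outcomes such as cortisol, fit the same model after log transformation. Unweighted GEE is not an equal substitute, because it generally needs dropout to be completely at random.
4. Do not use Friedman for the group comparison. Keep Kruskal-Wallis (with two arms, the rank-sum test) for single-visit or change-score comparisons.
5. Reconcile the statement that "outcome data will be complete" with the attrition expected in the sample size paragraph.

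Cost: a change of wording and slightly more modelling in standard software, with no new data. The model relies on a missing-at-random assumption, which should be stated.

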## Methods and Design

FNI is a randomized controlled trial designed to determine the short- and long-term physiological and behavioral effects of a family nurture intervention on preterm infant development. The intervention takes place over the course of the NICU stay. FNI is designed to help the mother and her preterm infant engage in interactive biologically important activities and behaviors that enhance the maternally-mediated sensory experiences of preterm infants, as well as the infant-mediated sensory experiences of the mother. Extended family members are also engaged and encouraged to adopt both a supportive and supplementary role in the process. Our primary hypotheses are that the FNI group will have increased infant brain activity as assessed by electroencephalogram (EEG) power and better basic neurobehavioral function close to term and at 18 months CA as compared to the Standard Care (SC; described below) group. Our secondary hypotheses are that the FNI group will have decreased stress responses in mother and infant at four months CA, fewer maternal anxiety and depressive symptoms after discharge from the NICU, as well as better maternal attachment and support systems as compared with the SC group. In addition to the aforementioned measures, we are also collecting samples of infant blood, breastmilk and stool samples from mother and infant.

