### Participants

The study setting is a high acuity neonatal intensive care unit at Morgan Stanley Children's Hospital in New York, NY. The intervention is conducted during the infant's stay in the NICU. All follow-up assessments are conducted at adjacent facilities to the hospital at Columbia University Medical Center.

Families are eligible for recruitment if the infant is born a singleton or twin in the hospital between 26 and 34 weeks post-menstrual age (PMA), if the mother has no history of drug addiction or psychosis or other severe mental illness, if the mother understands and speaks English, and if there is at least one adult other than the mother in the home. Infants are excluded from the study if their birth weight is below the third percentile for gestational age or if there are significant congenital defects. Families are excluded if there is not at least one adult other than the mother in the home, since in such cases the critical family support component of the intervention could not be completed or evaluated (see Family Support Sessions below).

Recruitment is undertaken by a trained research assistant (RA). The RA reviews birth records daily. After obtaining permission from the attending physicians of both mother and infant, the RA invites qualifying families in the Obstetrics Ward or NICU to participate in the study. The RA describes the study procedures to the parents, including the randomization process, and obtains a written consent form from those enrolling. Mothers wishing to think about the study or talk it over with family members are encouraged to make a decision within 24 hours so that the intervention can start as early as possible.

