#### Psychological Assessments of FNI and SC Mothers

Mothers in both groups are assessed by means of a wide-range of psychometric instruments. As summarized in Table 2 these include indices of anxiety, depression, temperament, personality, attachment, stress, and social support, that are assessed near enrolment and before group assignment and again at Term, 4, 12, 18, and 24 months CA. Prior to randomization, mothers are administered questionnaires to assess their *levels of anxiety *(Speilberger State-Trait Anxiety Inventory, STAI [53]), and *depressive symptoms *(Center for Epidemiological Studies Depression Scale, CES-D [54]). These questionnaires must be completed by the mother before her group assignment, as her responses could be affected by the assignment itself. After group assignment, the quality of the mother's attachment is assessed using the Adult Attachment Interview (AAI) [55]). The status of inhibitory vs. approach systems (Behavioral Inhibition System-Behavioral Approach System, BIS-BAS, [56]), and Mom's Support Circle [Additional File 1] are assessed after group assignment and again at Term, 4, 12, 18, and 24 months CA. Finally, questionnaires that focus on the *mother's sense of stress *(Parenting Stress Index, PSI, infant [57,58]), availability of *social support *(Norbeck Social Support Questionnaire, NSSQ [59]), efficacy as a mother (Maternal Self-Efficacy Scale, MSES [60]), and temperament (Adult Temperament Questionnaire, ATQ [61]) are administered at the 4,12, 18, and 24 month follow-up visits.

**Table 2 T2:** Outcome measures

Parental measures	Abbreviation		Ref	Measurement	Time(s) administered
**State-Trait Anxiety Inventory**	STAI	◆	[53]	Mother's anxiety level generally and at the current moment	E1, D, T and 4, 12, 18, 24 mo. CA
**Center for Epidemiological Studies Depression Scale**	CES-D	◆	[54]	Mother's depressive symptomology during the past week	E1, D, T and 4, 12, 18, 24 mo. CA
**Behavioral Inhibition System-Behavioral Approach System**	BIS-BAS	◆	[56]	Mother's aversive and appetitive motivation	E2, T and 4, 12, 18, 24 mo. CA
**Adult Temperament Questionnaire**	ATQ	◆	[61]	Mother's temperament	4, 12, 18, 24 mo. CA
**Parenting Stress Index (short version)**	PSI	◆	[57]	Mother's parenting stress	4, 12, 18, 24 mo. CA
**Maternal Self-Efficacy Scale**	MSES	◆	[60]	Mother's feelings of effectiveness in parenting	4, 12, 18, 24 mo. CA
**Adult Attachment Interview**	AAI	◆	[55]	Mother's perception of her intimate relationships	E2

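### The FNI comparison on the primary 18-month Bayley-III is an unadjusted t-test that leaves collected baseline data unused, and the only covariate model described cannot stand in as the adjusted FNI effect

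*Protocol article*

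**What the plan says.** All references are to the protocol article.

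- **Group comparison.** Planned analyses states: "Outcomes for the two study groups including infant EEG measures, stress and development, and maternal stress and depression will be compared at each measurement interval". For continuous data this is done "using independent t-tests for differences between means for continuous data", with a Bonferroni correction. The intervals listed include 18 months.
- **Covariate model.** The same section adds: "Generalized linear models will be used to assess the variability in infant development, as measured by Bayley-III Scales at 18 months CA". The next sentence gives its content: "This variability is explained by repeated maternal and infant psychological and neurological factors after controlling for baseline family socio-demographic characteristics". No group term is named, and family socio-demographics are the only baseline controls.
- **Status of the outcome.** Methods and Design includes in the primary hypotheses "better basic neurobehavioral function close to term and at 18 months CA as compared to the Standard Care" group. Primary and Secondary Outcome Measures lists the 18-month Bayley-III among the primary measures.
- **Timing and role of the repeated factors.** The maternal psychological instruments are "assessed near enrolment and before group assignment and again at Term, 4, 12, 18, and 24 months CA". Methods and Design predicts that the "FNI group will have decreased stress responses in mother and infant at four months CA, fewer maternal anxiety and depressive symptoms".
- **Baseline information.** Under Participants, infants qualify if "born a singleton or twin in the hospital between 26 and 34 weeks post-menstrual age (PMA", so gestational age at birth and twin status are known for each infant. STAI and CES-D are completed before assignment.

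**The concern.** Two things stand out when these statements are read together.

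First, the test that answers the trial's question on this primary outcome adjusts for nothing. Eligibility covers eight weeks of gestation, and under Potential limitations the article itself names variation in infant health as something that may influence outcomes independently of the intervention. Baseline variables that are plausibly prognostic for 18-month development are recorded and then left out of the comparison. What is lost is precision.

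Second, the one model that does carry covariates is not built to estimate a treatment effect. Many of its predictors are measured after assignment and are of the kind FNI is meant to alter. The article does not label the model's role. Because it is the only adjusted analysis of a primary outcome, there is a risk that it will later be presented as the adjusted FNI result, which it is not.

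**Working it through.** **Inputs from the document** (Table 1 and the sample-size paragraph under Participants): Bayley-III reference SD 14; detectable difference 6.0; total N 174; two-sided alpha .05; power .80; equal allocation (3 FNI and 3 SC per block of six); attrition up to 40%; recruitment 260.

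**Input not in the document (assumption):** the share of Bayley-III variance explained by baseline covariates, R², taken as 10, 20 and 30%.

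**Step 1. Reproduce the plan's own figure.** d = 6/14 = 0.4286. A two-sample t-test at two-sided .05 and 80% power needs 86.4, so 87 per arm, total 174. This matches Table 1 exactly. The normal approximation gives 86 per arm, total 172. The sample size therefore belongs to the unadjusted group comparison and not to the generalized linear model.

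**Step 2. Power of the planned test.**
- N = 174 (87 per arm): 80.3%.
- Retained under the plan's own attrition: 260 × (1 − 0.40) = 156 (78 per arm): 75.8%.

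**Step 3. Power with baseline adjustment.** Adjusting for baseline covariates leaves the expected treatment effect unchanged and reduces the residual SD to 14 × √(1 − R²). The effective standardised difference becomes d / √(1 − R²).

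| R² (assumed) | Residual SD | Effective d | Power, N = 174 | Power, N = 156 | Total N for 80% |
|---|---|---|---|---|---|
| 0 | 14.00 | 0.429 | 80.3% | 75.8% | 174 |
| 0.10 | 13.28 | 0.452 | 84.2% | 80.1% | 156 |
| 0.20 | 12.52 | 0.479 | 88.2% | 84.5% | 140 |
| 0.30 | 11.71 | 0.512 | 91.9% | 88.9% | 122 |

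These figures treat infants as independent, test at .05 without the Bonferroni correction, and ignore the few degrees of freedom used by the covariates. Twin clustering and Bonferroni would lower every row.

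**Step 4. Can the generalized linear model supply the adjusted effect?** This is settled by the text.
- As written it contains no group term, so it yields no FNI coefficient.
- Its predictors are repeated factors. The maternal series has a pre-assignment measurement but continues at Term, 4, 12, 18 and 24 months CA. The infant EEG (34 to 40 weeks PMA) and NNNS (36 and 40 weeks) are scheduled in Table 2 during or after the NICU intervention.
- The hypotheses predict that FNI changes brain activity, neurobehaviour, stress responses, and maternal anxiety and depressive symptoms. Were a group term placed beside such factors, its coefficient would leave out whatever part of the effect runs through them. It would not be the total FNI effect.

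**The case against.** The strongest reply is that the plan already has a sound analysis. Randomisation makes the t-test an unbiased comparison, Table 1 is sized on it, and leaving out covariates is neither an error nor a contradiction. The generalized linear model is worded as explaining variability. An association model needs no group term and may properly use post-assignment predictors. This is also a journal article, so a full covariate list may sit in a document not shown.

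Most of this stands. The t-test is valid apart from attrition and twin clustering, and the absence of a group term from an explanatory model is not in itself a fault.

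A reader might infer something stronger: that the FNI effect on Bayley-III cannot be estimated, or that the plan will produce an estimate diluted toward zero by conditioning on mediators. The document does not support either. The 18-month group comparison is planned separately, and the model is nowhere called the treatment analysis or the primary analysis. A diluted estimate would need a group term the article does not include, and its size would depend on mediated shares the article does not give.

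Two points survive. The article states the unadjusted test as the method, so the unused baseline information is a stated choice and not merely a gap. It also prints the predictor set of the generalized linear model without labelling the model's role.

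**Conclusion.** The concern holds in a limited form. The planned FNI comparison on 18-month Bayley-III is valid but gives up precision that costs nothing to recover, and the only covariate model described must not be reported as the adjusted FNI effect.

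The possible gain is about 4 to 12 percentage points of power at N = 174 and about 4 to 13 at 156 retained. At 156 the unadjusted test falls short of the 80% target (75.8%), and an R² of only 10% would just restore it (80.1%). This rests on the Table 1 difference and SD, on 40% attrition occurring in full, and on an assumed R² of 10 to 30% for which the document gives no figure. It is a recommended improvement and does not invalidate the planned test.

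**What to change.** 1. Make the FNI estimate for 18-month Bayley-III a prespecified linear model with group and baseline covariates only: gestational age at birth, twin status, pre-assignment CES-D and STAI, and family socio-demographics. The unadjusted difference can be reported beside it.
2. Allow for twins with a family-level term or cluster-robust standard errors. The Twins section recognises that the intervention cannot be applied independently within a pair but names no method. It restricts assessment to the first-born only at 4 and 12 months, so both twins can contribute at 18 months.
3. Label the existing generalized linear model as an exploratory association or mediation analysis, and state that it does not estimate the total FNI effect.

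The cost is analysis-plan wording, settled before group-level results are seen. No new data are needed, because each of these covariates is already recorded or known at enrolment.
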